### Study participants

Four hundred and ninety patients who participate voluntarily; our intention is to include at least 40% men.

#### Inclusion criteria

Adults, aged between 29 and 66 years, BMI between 29 and 40.99 kg/m^2^.

#### Exclusion criteria

Pregnancy (women), behavioral eating disorders, relevant gastrointestinal disease (ulcerative colitis, Crohn’s disease, celiac disease, digestive tract cancer), excessive alcohol consumption (>28 U or 280 g/week in men, >17 U or 168 g/week in women), cardiovascular event in the last 3 months or unstable cardiovascular disease, diabetes, polycystic ovary disease, treatment with any medication that could alter insulin sensitivity or body weight (corticosteroids, antipsychotics, antidepressants), pharmacological treatment for clinical or subclinical hypothyroidism, hyperthyroidism, depression, psychosis, microalbumin/creatinine ratio >100 mg/g or stage-IIIB or higher chronic kidney disease (glomerular filtration rate <45 mL/min), use of medication requiring frequent dose adjustments and low intellectual or mental functioning that could interfere with the participant’s compliance with the recommendations. If the result of the glucose overload test is blood glucose ≥200 mg/dL the participant is excluded if the physician opts to add medication or insulin to the dietary and physical exercise regime.

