**Methods/design:**

This field trial is located at primary care centers. The participants are adults aged 29 to 66 years, with a Body mass Index (BMI) between 29 and 40.99 kg/m^2^ and without diabetes. To date, 245 participants have been assigned randomly to the low-fructose diet intervention group (LFDI) at health centers in the western health service zone of Tenerife island, and 245 to the standard-diet control group (SDC) at health centers in the eastern health service zone. Recruitment is opportunistic and is carried out by physicians and nurses at participating health centers. Initially (baseline), and after 24 weeks of intervention, dietary records, physical activity, waist circumference, BMI, blood pressure, fasting blood glucose and insulin concentrations (HOMA2-IR) and lipid profile are recorded; blood glucose and insulin and lipid profile are also recorded 2 h after a 75-g glucose overload. After 48 weeks (24 weeks after the intervention), fasting blood samples are again obtained and a physical examination is performed. All tests and measures are repeated and recorded except dietary records, physical activity and oral glucose overload. Low-fructose diets are designed by calculating free and total (free + fructose associated with sucrose) fructose contents in standard diets, and removing foods with a fructose content in the highest quartile for the amounts in the standard diet.

Participants in both groups are prescribed a diet that contains 30 to 40% less than the participant’s energy requirements. The primary endpoint is change in HOMA2-IR between baseline and week 24, and other outcomes are change in HDL-cholesterol, LDL-cholesterol, triglycerides , waist circumference to height ratio and BMI. The secondary endpoint is change in HOMA2-IR between week 24 and week 48 together with the outcomes noted above. Comparisons between groups for variables used to indicate IR levels are done with a Student’s *t* test for unpaired variables or the Mann-Whitney *U* test if the distribution is not normal. Multivariate regression models will be used to control for confounding factors not accounted for in the study design, and for independent prognostic factors.

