### Randomization

Participants are randomized by health care zone. Patients in the low-fructose diet intervention group (LFDI) are assigned to health centers in the western zone of Tenerife island, and patients in the Canary Islands Health Service standard-diet control (SDC) group are assigned to the eastern zone of the island. This randomization system is used to prevent contamination bias. If patients randomized to both groups attended the same health center this source of bias would be difficult to avoid because many patients in the LFDI group are likely to have relatives or friends in the SDC group, and vice versa. Contamination could also occur between staff members at a given health center. Sixteen primary health centers are participating in this study; all of them belong to the same health care administration district (Gerencia de Atención Primaria de Tenerife). Given that the total area of the island of Tenerife is relatively small, the characteristics of the population served by all health centers are assumed to be similar. The longest distance between participating health centers is 64 km. All centers and staff provide the same suite of services. The variations between centers in the catchment population assigned and the numbers of patients under each staff physician’s and nurse’s care are similar. We therefore do not anticipate between-group differences in the baseline data or systematic biases in the results of the care provided at different centers.

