### Recruitment

Physicians and nurses recruited participants with an opportunistic method. To facilitate recruitment we designed a digital application for electronic medical records that make it possible to identify patients who could hypothetically be recruited on the basis of our inclusion and exclusion criteria. The first screen of the electronic medical record displays an alert indicating that the patient is potentially eligible for inclusion. The nurse or physician explains the nature and aims of the study to the patient, and if the patient expresses interest in taking part, the physician asks three questions about their motivation. If the patient answers “yes” to all three questions the nurse or physician asks them to sign the Informed Consent Form (see Additional file 1), and then gives the patient a brief Information Pack that includes four pages of a food diary in which the patient is asked to record all foods and beverages consumed each day during a 4-day period that includes one weekend day or holiday. The Information Pack also includes a sheet with instructions on how to record foods and beverages in the food diary (see Additional file 2). On the day that the patient signs the Informed Consent Form, an appointment is scheduled to review the food diary and complete the Case Record Form (CRF). At this appointment the physician or nurse carefully reviews all four daily food diary sheets with each participant to ensure accuracy regarding the types, sizes and portions of each food and beverage. During this appointment the participant is interviewed about their physical activity and the information provided is entered by the physician or nurse into the Minnesota Leisure-time Physical Activity Questionnaire form. Body weight, height and waist circumference are recorded, and blood pressure is measured twice and recorded as the average of the two values. At the end of this appointment the participants is given an appointment for a blood test (week 0). The blood sample is provided after an overnight fast, and is used to measure plasma glucose, insulin and lipid concentrations (total, LDL- and HDL-cholesterol and triglycerides). At week 0 we also record thyroid stimulating hormone (TSH), total thyroxine (T_4_) if TSH is altered, and urinary microalbumin/creatinine ratio (to rule out relevant thyroid or kidney disease). All participants undergo an oral glucose overload test (75 g) to record blood insulin, glucose and lipids 2 h later. All participating health center staff are reminded to use the same equipment in each appointment to record blood pressure, weight and height. All devices are calibrated regularly by the Canary Islands Health Service. Nonstretchable measuring tape is used to record waist circumference by situating the tape halfway between the lower margin of the last rib and the iliac crest with the participant breathing normally.

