
### Intervention

All participants sign an Informed Consent Form. The study was approved by the Ethics Committee of Nuestra Señora de La Candelaria University Hospital. The intervention (except for nutrition counseling), number of appointments and laboratory tests are the same in both groups.

Participants in the LFDI group are advised to eat a low-fructose diet designed on the basis of standard diets (1000, 1250, 1500, 1750, 2000, 2250, 2500 or 2750 kcal/day) recommended by the Canary Islands Health Service [18]. Low-fructose diets are designed by calculating free and total (free + fructose associated with sucrose) fructose contents in standard diets. Foods with a fructose content in the highest quartile for the amounts corresponding to the standard diet are removed from the standard diet. The format and graphical appearance of the information about the participant’s diet are identical in both groups. Physicians and nurses who prescribe the standard diets are unaware of which foods have been excluded from the low-fructose diets. To avoid contamination bias while recruitment is currently underway, the present report does not include information on the composition of the low-fructose diets.

Nutrition counseling and reinforcement take place at weeks 2, 4, 8, 12, 16 and 20. During this process we emphasize to participants the importance of involving in the intervention the person in the household who purchases and/or prepares food. At week 2, after the physician or nurse has reviewed the nutritional information, intervention via individualized nutrition counseling begins. At week 24 a second blood sample is obtained for analysis. Two weeks before week 24 the participants are given a new Information Pack containing the same materials as the initial Information Pack at the start of the study, with instructions on how to record foods and beverages consumed during 4 days (including one weekend day or holiday). On the day of the appointment to provide a new blood sample, the participant meets first with the physician or nurse to review their food diary in detail.

The schedule of enrollment, interventions and assessments, which is based on the Standard Protocol Items: Recommendations for Interventional Trials (SPIRIT) figure, is shown in Fig. 1 and the process for participant recruitment and follow-up is shown in Fig. 2.

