### Statistical analysis

Before-after changes in IR, laboratory indicators and anthropometric values are determined with Student’s *t* test for paired samples. Comparisons between the intervention and control groups for variables indicative of IR are done with Student’s *t* test for independent samples when the frequency distribution is normal, or with the Mann-Whitney *U* test when the distribution is not normal. For these comparisons multiple linear or regression models are used as appropriate to detect possible confounders or independent prognostic factors for IR that are not controlled for in the trial design. Student’s *t* test for paired samples will be used to analyze changes between week 0 and week 24 in the main outcome variables in each group (HOMA2-IR, fasting blood glucose and insulin, and these same measures after an oral glucose overload) and the secondary outcomes (fasting LDL-cholesterol, HDL-cholesterol and triglycerides, and these same measures after a glucose overload; waist circumference, waist to height ratio, BMI and blood pressure). To verify compliance with the recommended diets the same analysis will be done for total calorie intake and individual nutrient intakes. These analyses will record results for the variables noted above between week 24 and week 48, and between week 0 and week 48. Student’s *t* test for independent samples will be used to analyze the differences between groups observed from week 0 to week 24 for the variables noted above. As potential confounders we will consider calorie intake, variations in nutrient intakes other than fructose, and physical activity. If differences are detected between groups at the start of the study in HOMA2-IR, any nutrient intake or physical activity, appropriate adjustment will be used in the outcomes analysis. An intention-to-treat analysis will be done taking into account losses to follow-up, and using the most recent changes and measurements available for participants who did not complete the study. All hypothesis tests will be two-sided with a significance level of *p* < 0.05, and all statistical analyses will be done with the NT Professional v. 21.0 (IBM) statistical package (SPSS) for PCs in a Windows environment. More specific information about the trial and protocol is summarized in the Standard Protocol Items: Recommendations for Interventional Trials (SPIRIT) Checklist (Additional file 5).

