## Discussion

The aim of this study is to evaluate the effectiveness of a low-fructose/sucrose diet compared to a standard diet in lowering IR in obese patients without DM after an intervention period of 24 weeks. Overall reductions in fructose/sucrose consumption are evaluated with no distinction between added sweeteners and sugar naturally present in foods. A diet low in foods with natural fructose content is prescribed for the intervention group, but participants in both groups are instructed to refrain from consuming foods with added sugar. This approach is used because it reflects the usual care offered at participating health centers, and in an effort to ensure comparable food intakes in kcal/day in both groups. To evaluate the difference in fructose intake our reference is the mean value from four daily food diary records from the end of the intervention period (week 24) compared to four daily food diary records at week 0. Although the evidence at present is insufficient to claim that four food diaries are sufficient to provide a reliable analysis of fructose or sucrose intakes, most studies that have estimated these intakes to date have used 24-h recall or (usually four) food diaries [27].

At present, the amount of fructose intake that could be harmful to health is unknown. A trial such as this one, carried out in the primary care setting, should provide valuable information for future efforts to control IR. Because the restricted calorie diet prescribed for our participants is similar in both groups, we expect to see similar weight reductions in both. Our hypothesis is that under our trial conditions, the reduction in IR will be greater in the group with the low-fructose diet than in the SDC. Accordingly, if the dietary intervention being tested, i.e., a diet low in fructose/sucrose, is able to reduce IR, the results – if translated into regular clinical practice – could provide a hitherto unavailable tool to prevent type-2 DM.

A potential limitation of this type of study is the likelihood that many participants will under-report some of their food intakes, as has been shown for persons with obesity. We will analyze the energy intake:basal metabolic rate ratio with a cutoff value of 1.16 for women and 1.19 for men to determine whether participants are under-reporting any food intakes [28].

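### Minor: exclusion after a glucose-load value of 200 mg/dL or more turns on the physician's choice to medicate, and different physicians make that choice in each arm, so retention of these participants can differ by arm

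*Protocol article*

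**What the plan says.** - **The rule.** In the protocol article, Exclusion criteria, a glucose-load value of 200 mg/dL or more leads to exclusion on one further condition: "the participant is excluded if the physician opts to add medication or insulin to the dietary and physical exercise regime". The section gives no criterion for that choice.
- **Who decides.** Randomization: "Participants are randomized by health care zone". Low-fructose patients attend western centers and control patients attend eastern centers, partly to keep staff in the two arms apart.
- **When.** Recruitment places the test with the week-0 blood sample, after consent: "All participants undergo an oral glucose overload test (75 g) to record blood insulin, glucose and lipids 2 h later". According to the Abstract it is repeated at week 24. The exclusion rule does not say which of the two tests it refers to.
- **Adjustment.** Under Statistical analysis, "multiple linear or regression models are used as appropriate to detect possible confounders or independent prognostic factors for IR". A separate sentence provides for adjustment if the groups are found to differ at the start in HOMA2-IR, any nutrient intake or physical activity. Two-hour glucose is not named. The section also commits to intention-to-treat analysis using the latest available measurements.
- **Recruitment status.** The Abstract reports "To date, 245 participants have been assigned randomly to the low-fructose diet intervention group (LFDI" and the same number in the control group. The Intervention section withholds the diet's composition with the words "To avoid contamination bias while recruitment is currently underway".

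**The concern.** Two participants with the same 2-h value can be handled in opposite ways, one excluded and one retained. If the same physicians saw both arms, uneven use of this discretion would tend to balance out. Here it cannot, because the center fixes the arm before the test is done and each arm has its own physicians. If one zone's physicians start drugs more readily, that arm keeps fewer participants with the highest 2-h glucose.

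The endpoint is the change in HOMA2-IR. Such a difference in retention would bias the comparison only if these participants change differently from the rest over 24 weeks. At stake is a small selection effect that arises after the arm is fixed, and that the planned baseline adjustment does not specifically address.

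Timing is a second, separate point. Because the rule is not tied to the week-0 test, it does not rule out removing someone for a week-24 result, which would be a post-intervention exclusion.

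**Working it through.** The document gives no figure to reproduce here, so the check is a bounding calculation.

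**Inputs from the protocol article, Design:** 245 per arm, 20% dropout, 5% significance level (two-sided according to Statistical analysis), 80% power.

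**Assumed inputs, not in the document:**
- share *p* of participants at 200 mg/dL or more: 2-8%, that is 245 × 0.02 = 4.9 to 245 × 0.08 = 19.6 per arm;
- difference *d* between these participants and the rest in change in HOMA2-IR: 0.5-1.0 SD in absolute size, sign unknown (zero is also possible and gives no shift);
- exclusion rates *a* and *b* in the two arms;
- dropout unrelated to the 2-h value.

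**Step 1: detectable difference.** Completers per arm are 245 × 0.80 = 196. The detectable difference is (1.960 + 0.842) × √(2/196) = 0.283 SD.

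**Step 2: shift from unequal exclusion.** With exclusion rate *e*, the retained share of high-glucose participants is p(1 − e)/(1 − pe). The shift in the between-arm difference is d × [p(1 − b)/(1 − pb) − p(1 − a)/(1 − pa)].

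Worked case with p = 0.08, d = 1, a = 0.8, b = 0.2:
- arm with b = 0.2: 0.064/0.984 = 0.0650;
- arm with a = 0.8: 0.016/0.936 = 0.0171;
- shift = 0.0650 − 0.0171 = 0.048 SD.

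| Exclusion rates | Low end (p = 2%, d = 0.5) | High end (p = 8%, d = 1.0) | As share of 0.283 SD |
|---|---|---|---|
| equal | 0 | 0 | 0% |
| 60% vs 40% | 0.002 SD | 0.016 SD | 1-6% |
| 80% vs 20% | 0.006 SD | 0.048 SD | 2-17% |
| 100% vs 0% (extreme bound) | 0.010 SD | 0.080 SD | 4-28% |

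**Step 3: clustering.** With 16 centers, 392/16 = 24.5 completers per center. The design effect is 1 + 23.5 × ICC, which is 1.235 at an assumed ICC of 0.01 and 2.175 at 0.05. The detectable difference becomes 0.283 × √1.235 = 0.315 to 0.283 × √2.175 = 0.417 SD. The 0.048 SD case is then 0.048/0.315 = 15% to 0.048/0.417 = 11% of it.

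**Step 4: precision cost of the restricted analysis.** If 2%, 5% or 8% are omitted, 196 completers per arm become 192, 186 or 180. The detectable difference becomes 2.802 × √(2/192) = 0.286, 2.802 × √(2/186) = 0.290 or 2.802 × √(2/180) = 0.295 SD.

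**The case against.** The strongest reply is that no harm is shown. Randomization describes one administrative district with the same services throughout, and expects no systematic bias between centers. HOMA2-IR is calculated from fasting values, so a high 2-h glucose does not by itself imply a different 24-week change, and a pure difference in baseline level cancels in a change score. The 0.5-1.0 SD input is unsupported and has no known direction. The rule also has a sensible purpose, since it keeps out people who start glucose-lowering drugs. Other judgement-based criteria share the same weakness, which comes from allocating by zone. Adjustment for a detected difference in baseline HOMA2-IR is planned, and the general regression models could include 2-h glucose. All of this stands, and it is why the point is minor. It does not make the discretion uniform across arms: the expectation of similar centers is an assumption, not a common rule for this decision.

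Three stronger readings are tempting, and the document supports none of them.
- A reader might infer that the rule contradicts the description of the trial population as "in lowering IR in obese patients without DM after an intervention period of 24 weeks". Diabetes is a separate exclusion, and no section defines a single glucose-load value of 200 mg/dL or more as diabetes. The contradiction would need an outside diagnostic criterion.
- A reader might infer that physicians exclude with the arm in mind. They prescribe their zone's diet and may know the arm, but the document does not say so. It does say that the diet sheets look alike and that prescribers of the standard diet do not know which foods were removed from the other.
- A reader might infer that week-24 exclusions are planned. The text only fails to rule them out, and the intention-to-treat commitment points the other way.

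**Conclusion.** The point holds as a minor one. Exclusion at this step is discretionary, follows consent, and is decided by different physicians in each arm, so retention of participants at 200 mg/dL or more can differ by arm. Whether it does is not shown, and neither is which arm would gain. The likely shift is about 0 to 0.05 SD against a detectable difference of about 0.28 SD. That range rests on assumed prevalence, an assumed difference in HOMA2-IR change and exclusion rates no further apart than 80% versus 20%. The 0.080 SD figure needs every input at its extreme together and is a bound, not an expectation. The reason to act is that a complete check on this step is available at almost no cost. Reporting exclusion counts per arm and naming 2-h glucose as a covariate are reporting or analysis-plan details, and their absence here is no fault.

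**What to change.** 1. **Add a restricted analysis.** Analyse the primary endpoint in participants with week-0 2-h glucose below 200 mg/dL in both arms. The rule cannot act below that value, so the set is the same whatever the physicians chose. The week-0 test is planned for all participants, so no new data are needed. The cost is 2-8% fewer participants (assumed prevalence), with the detectable difference rising from 0.283 to 0.286-0.295 SD.
2. **Tie the exclusion to the week-0 test.** One sentence would say so, and would add that nobody leaves the intention-to-treat set because of a week-24 glucose-load result. This costs nothing.
3. **Optional, if recruitment is still open.** Exclude on the week-0 value of 200 mg/dL or more alone, identically in both zones, and leave treatment to the physician. This is a trade-off. It drops people managed by diet alone from a trial meant to reflect real-life conditions. A change made with most participants already assigned would also leave two eligibility rules in one trial. Item 1 works either way.

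People already excluded under the rule can probably not be recovered, but the restricted analysis does not need them.
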